### Outcome measures

#### Physical activity

Time spent in moderate to vigorous intensity PA, as well as total movement, will be assessed over 7 days using two Actical accelerometers worn on the wrist and the hip. The MiniMitter Actical is the most widely used and validated accelerometer in studies of children and adolescents [54,9]. Seven days of accelerometer measurement are recommended for the purposes of acceptable measurement of moderate to vigorous PA [9]. Total weekly PA as well as weekend PA and after school weekday PA will be assessed.

#### Energy expenditure

Total energy expenditure (TEE) will be measured using the DLW technique [55,56]. This is the gold standard method for assessing free living TEE and has been used extensively in children and adolescents [57]. Due to the nature of the study with children being assessed in the home at different points in the day, in non-fasted states, a measured RMR estimate is not deemed a suitable. BMR will therefore be predicted from the subjects sex, age, weight and height using Schofields's equations for children aged 10–17 yrs of age [58]. Predicted BMR has been shown to have good agreement with measured RMR by indirect calorimetry in children of all ages [59,60].

From these two energy expenditure measurements, the habitual physical activity level (PAL) is calculated as the ratio of TEE: BMR. The PAL ratio is a convenient way of adjusting energy expenditure for age, sex, weight and body composition and is a widely accepted measure of habitual PA [61,62]. The DLW technique involves collection of a daily urine sample for 10 days. These samples will be stored in Perth, and sent to Brisbane for subsequent analysis.

#### Motor coordination

Motor competence will be assessed using Movement Assessment Battery for Children-2 (MABC-2) [63]. The MABC-2 comprises 8 tasks, three measuring manual dexterity, 3 measuring aiming and catching and 2 measuring balance. Age norms based on a standardisation sample of 1,172 children are used to determine a standard total score (*M *= 10, *SD *= 3). Separate standard scores can be determined for each of the sub-tests. In addition to the total score, a set of qualitative observations allows the examiner to record the child's performance characteristics during the testing. Cut-offs for impairment scores are at or below the 5th percentile for definite motor difficulties, whilst scores above the 5th percentile but below the 15th percentile suggest borderline difficulties. Minimum value of the test-retest reliability of the original MABC is 0.75 and the inter-tester reliability is 0.70. The original MABC has been found to correlate well with other movement tests [64,65]. Assessment of MABC2 will be conducted by a second research officer blind to participant condition.

#### Adiposity

Percentage body fat will be determined from the measurement of the ^18^O dilution space, which is calculated as part of the DLW technique for measuring energy expenditure. Taking into account the fact that ^18^O overestimates total body water by 1% [66], and using published total body hydration constants from children of different ages [67], fat-free mass can be calculated from total body water. Fat mass is calculated as the difference between total body weight and fat-free mass and expressed as a percentage.

Waist circumference measurements will be taken and age and sex adjusted BMI z-scores will be calculated to enable comparison with state-wide surveys (WA, QLD).

#### Child Self-Perceptions

Harter's Self-Perception Profile for Children [68] will assess self-perceptions across domains of Scholastic Competence, Social Acceptance, Athletic Competence, Physical Appearance and Behavioural Conduct, and it also includes a subscale designed to evaluate global self-worth that assesses self-esteem independent from the competence domains. It has been validated in samples of children from a wide range of cultural backgrounds, including in Australian children and has high levels of internal consistency ranging from .74 to .92 [68].

#### Attitudes to technology

Attitudes to technology will be assessed using Webster et al's measure of 'flow' which we have previously shown to have acceptable reliability when used with children aged 10–12 years (Cronbach's alpha .82) [69]. In addition we will use Deane et.al's measures to assess the Technology Acceptance Model factors of 'ease of use' and 'usefulness of technology' which show acceptable to good internal reliability (.67 and .82) [70].

#### Attitudes to PA

Attitudes to PA will be assessed using the revised Physical Activity Enjoyment Scale [71]. Internal consistency, test-retest reliability and construct validity has been demonstrated [72-74].

#### Leisure activity

To provide descriptive information on the type of activities performed, participants will use a modified version of the previous-day PA recall (PDPAR) in the form of a diary for 7 days. In the PDPAR the predominant activity for 30 minute blocks during waking hours is recorded. Use of the PDPAR over several consecutive days, in the form of a diary has also been shown to be valid, against measures of accelerometry, and feasible [75]. From this diary, displacement of activity categories will be calculated.

### Covariates

#### Season

Prior PA research has identified significant differences between summer and winter seasons and interactions with sex (more reduction in PA in winter in girls) [21]. The potential seasonal effect will be allowed for in the design by having a balanced ordering of game conditions and a staggered start to cover the school year.

#### Electronic game experience

Computer and electronic game and interface experience which could confound the effect of the game condition will be measured using a questionnaire based on our prior studies and a large USA study [29].

#### Sex

Equal numbers of boys and girls will participate. Boys and girls are known to differ in the nature of their electronic game exposure and in the other measures being taken. The games selected will be based on discussions with children to ensure desirability by both girls and boys, as per our successful pilot study.

### Procedure

Following screening, participants will be randomly allocated to an order of conditions by selection of an opaque sealed envelope. A balance of orders across the year will be achieved by having 4 sets of the 6 possible order permutations in each year cohort of 24, repeated over three years. After informed consent/assent from parent and child, a research officer (RO) will visit the home and instruct parent and child in baseline assessments. This visit will include measurement of resting energy expenditure, explanation of the DLW method and initial dosing, explanation of the assessment and questionnaire. The RO will return after 10 days to collect baseline assessments and set up the electronic game condition. This will involve either removal of all electronic games or setting up electronic game equipment and instructing parent and child in its use. Follow-up phone calls will be made the next day and after 6 days to ensure game equipment is working correctly. Towards the end of the 6th week in a condition the RO will visit again to set up the DLW and PA assessments. After 8 weeks the RO will collect DLW samples and completed measures and set up the next condition. After all 3 conditions a debriefing interview with parent and child will be conducted to gain qualitative details on the trial. The family structure including number, age and sex of siblings will be recorded, and the behaviour of siblings during the trial will be assessed at debriefing interview. Assessment will be scheduled to avoid school and public holidays where possible. Individualised reports will be provided to participants.

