### Participants

36 boys and 36 girls (10–12 years of age) will be progressively recruited by mass media, community newsletters and local school notices. This age group has been selected as they are able to provide detailed information in diary and questionnaires, have a high use of electronic games and are developing activity patterns pre-puberty which may track into adulthood. Recruitment will be staggered over three years and targeted to enable participation of equal numbers of males and females, and children representative of a spread of socio-economic status, electronic game experience and motor competence Volunteers will be screened to ensure they are willing to participate after being informed of the full study responsibilities and meet the inclusion and exclusion criteria. Inclusion criteria are: aged 10–12 years at start of study and able to use electronic games on most days. Children will be excluded if they have a diagnosed disorder likely to impact their study participation, movement or electronic game use (other than developmental coordination disorder), live in a shared care arrangement where the child spends a significant amount of time in different houses and is unable to maintain game access condition, or live remote to the University campus. In 2009, 12 boys and 12 girls will be tested, with equal numbers tested 2010, and 2011.

For power calculations, daily moderate/vigorous PAL was estimated at 115+30 mins with a minimum effect size of 15 mins considered important based on effects in prior studies by us and others [51]. If the variation in the PA level between repeated time points in each individual is normally distributed with standard deviation 30 mins, and the true effect of game condition is 15 mins, a study with 72 subjects will reject the null hypothesis that this response difference is zero with probability (power) 0.986. The Type I error probability associated with this test of this null hypothesis is 0.05. If the Type I error is lowered to 0.01 to account for 'repeated' contrasts between conditions, the power is 0.943 [52]. We [51] have had a compliance rate of 95% for DLW data collection and 92% for accelerometry, and both measures have been widely used in studies of 50 to 100 children [53,9]. We have allowed for 10% attrition in data.

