### Analysis

To examine hypotheses 1 (that PA and energy expenditure will be reduced when children have access to traditional electronic games) and 2 (that PA and energy expenditure will be greater with new active electronic games, but still less than no games) a 4 (baseline and 3 game conditions) × 2 (sexes) repeated measures ANCOVA analysis with pre-specified contrasts will be conducted for each PA and energy expenditure variable. Prior game experience will be used as a covariate. A critical alpha level of 0.01 will be used to balance type 1 and type 2 errors.

To assess hypothesis 3 (that there will be a stronger effect on children with poor coordination skills, high adiposity, poor social confidence, more positive attitudes to technology and less positive attitudes to PA), separate multiple linear regression analyses for both traditional sedentary electronic and new active electronic games will examine the importance of individual characteristics on activity levels (total minutes of overall moderate/vigorous PA). Sex and amount of moderate/vigorous PA at the end of the no game period will be included as baseline covariates for the assessment of the independent effect on PA of; motor competence, adiposity, perceived athletic competence and attitudes to technology. To assess if individual characteristics may impact differently upon the relationship between PA and traditional sedentary electronic versus PA and new active electronic games, beta coefficients and associated 95% confidence intervals, and proportions of total variance explained by these variables, will be compared between the two models.

To assess hypothesis 4 (that all electronic games will displace active non-electronic leisure activities) the impact of the three study conditions on time spent in four outside school activities (reading, watching TV, using computers, playing sports and non-organised physical activity) will be examined using a 3 (no electronic games, traditional electronic games, active electronic games) ×2 (sex) repeated measures MANOVA with weekly minutes in each activity as the dependent variables.

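### Balance of condition orders is guaranteed per yearly cohort but not within sex; a minor gap, and cheap to close

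*Protocol article*

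**What the plan says.** In the protocol article:

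- **Procedure.** Allocation is by envelope: "participants will be randomly allocated to an order of conditions by selection of an opaque sealed envelope". Balance is defined at the level of the year: "4 sets of the 6 possible order permutations in each year cohort of 24", in each of three years. Sex is not mentioned in this rule.
- **Participants.** Sex numbers are fixed each year: "In 2009, 12 boys and 12 girls will be tested, with equal numbers tested 2010, and 2011".
- **Season (under Covariates).** Earlier research is cited for "significant differences between summer and winter seasons and interactions with sex (more reduction in PA in winter in girls". Season is to be handled through the design, by balanced ordering together with staggered starts.
- **Analysis.** Hypotheses 1 and 2 are tested with a model crossing baseline and the three conditions with sex: "2 (sexes) repeated measures ANCOVA analysis with pre-specified contrasts". The one covariate named is prior game experience. No period, order or season term is named.
- **Design and Aims.** None of the four numbered hypotheses is a sex-by-condition effect.

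**The concern.** The article expects season to act differently in girls and boys, and it names balanced ordering as part of the protection. The balance that it guarantees is over 24 children of both sexes. Over all children, each condition falls equally often in each period, so a common period effect cancels from the overall condition contrasts. Among boys alone or girls alone, that cancellation is not guaranteed. If one sex happens to get a condition more often in a late period, any change in activity over time enters the sex-specific condition effects and their difference. The named model has no term to absorb it. What is at stake is the precision of the sex-by-condition contrast and of any condition effects reported by sex.

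**Working it through.** **Inputs.** From the article: 24 children per cohort (12 boys, 12 girls), each of six orders used four times, three cohorts, 72 children; important effect 15 min; SD 30 min. Assumed, because the article gives no size: an activity drift of 15 min from first to last period.

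**1. Reproduce the stated power, to learn what the 30 min is.** For a two-sided paired t-test with 71 degrees of freedom, the noncentrality is 15/(30/√72) = 4.243. Power is 0.987 at alpha 0.05 (stated 0.986) and 0.941 at alpha 0.01 (stated 0.943). Taking 30 min as the SD at each time point, uncorrelated, gives 0.841 and 0.638. So 30 min is the SD of the within-child difference.

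**2. Standard errors.** Overall contrast: 30/√72 = 3.54 min. Sex-by-condition contrast: 30 × √(1/36 + 1/36) = 7.07 min.

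**3. Chance imbalance if sex is ignored.**
- Probability that every order splits two boys and two girls in one cohort: C(4,2)^6 / C(24,12) = 46,656 / 2,704,156 = 0.017.
- Boys having a given condition in period 1, over the trial: expected 12 of 36, 95% range 8 to 16.
- In simulation, about 71 to 72% of allocations have at least one of the nine condition-by-period cells for boys off by 3 or more.

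**4. Error in the sex-by-condition contrast, drift common to both sexes.** With period effects 0, 7.5 and 15 min, the period part of a difference between two conditions is ±7.5 in four orders and ±15 in two.
- Mean square: (4 × 56.25 + 2 × 225)/6 = 112.5. Finite-population variance: 112.5 × 24/23 = 117.4.
- Variance of the boys' mean in one cohort: (117.4/12) × (1 − 12/24) = 4.89. The girls' mean is its negative, so the difference has variance 4 × 4.89 = 19.6.
- Over three cohorts: √(19.6/3) = 2.55 min. The 95th percentile of the absolute error is 1.96 × 2.55 = 5.0 min.
- A simulation of 20,000 trials gives 2.56 and 5.0 min. If one period differs by 15 min instead of a linear drift, it gives 3.0 and 5.8 min.
- The error scales with the drift: 30 min gives about 5.1 and 10 min.

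**5. Drift in girls only.** This is nearer to the cited interaction. The error in the sex-by-condition contrast is that of the girls' mean alone: √(4.89/3) = 1.28 min. In the overall contrast it is half of this, 0.64 min, against a standard error of 3.54 min.

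**6. After the fix.** Two sets of six per sex make 12 boys and 12 girls, still four sets and 24 children. Each condition then falls four times in each period within each sex and cohort. With complete data, the period error is zero for a common or a sex-specific period effect.

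**7. Period terms alone.** If orders are drawn without regard to sex but period is modelled, the variance of the sex-by-condition contrast exceeds that under full balance by about 1.5% on average (95th percentile 5%).

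**The case against.** Four objections have force.

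- **Silence is not a statement.** A reader might infer that boys and girls draw from one pile. The article does not say so. Four sets for 12 boys and 12 girls fit two sets per sex equally well, and a condensed article may leave stratification to the full protocol. The text supports only that balance within sex is neither stated nor guaranteed.
- **The contrast is not a hypothesis.** A reader might take the equal sex numbers to mean that the trial was sized to study sex effects. The power calculation covers one within-child contrast in all 72 children, and no numbered hypothesis concerns sex by condition.
- **Confounding is too strong a word.** The imbalance arises by chance and has mean zero. At a 15 min common drift, total uncertainty rises from 7.07 to √(7.07² + 2.55²) = 7.52 min, about 6%. If the 30 min excludes period effects, an unadjusted analysis would carry them in its residual and report about √(900 + 112.5) × √(2/36) = 7.50 min. So precision is lost, but validity is largely kept.
- **Period is not season.** A reader might treat first-to-last drift as a winter-to-summer shift. Starts are staggered, so the two differ, and nothing in the article supports a uniform drift of 15 or 30 min.

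What remains is that the article itself invokes a sex-dependent season effect, puts sex in the model, names no period or season term, and states a balance rule that does not protect comparisons within sex.

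**Conclusion.** The point holds as a minor design improvement. For an assumed 15 min drift common to both sexes, and orders drawn without regard to sex, the added error in the sex-by-condition contrast has SD about 2.5 min, or 2.55/7.07 = 0.36 of its standard error. A girls-only drift of the same size gives about half of that. The overall condition contrasts, which carry hypotheses 1 and 2, are almost unaffected: zero error for a common drift and 0.64/3.54 = 0.18 of a standard error for a girls-only drift. The drift is an assumption, and the results scale with it. No stated figure is wrong. The article does not support the stronger reading that the sex comparison is systematically biased.

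**What to change.** 1. In each yearly cohort, allot two of the four sets of six orders to boys and two to girls, from separate envelope piles. If this is already done, say so in the Procedure section.
2. Add period and sex-by-period terms, over the three condition periods, to the repeated measures model. This removes most of the error even if allocation cannot be changed.

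**Cost.** N stays at 72 and the stated power is unchanged. The costs are a second envelope pile and four model degrees of freedom (two for period, two for sex by period). Balance of orders across the year is also slightly looser if boys and girls enrol at different times. Forcing equal numbers of each sex within every block of six would avoid that, but it would need recruitment quotas finer than the yearly ones the article sets, so it is not part of this request.

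**Limit.** Balance within sex removes period imbalance. It balances season only so far as start dates are also spread within each sex.

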### Trial flow

Figure 2 provides an overview of the trial flow. Following recruitment, screening and consent, participants are randomised to an order of electronic game conditions. After baseline assessments participants are setup in their first condition and are assessed at the end of the 8 week condition. Participants are then set up in their second condition for 8 weeks and then their third condition for 8 weeks, again with assessment occurring at the end of each condition.

**Figure 2 F2:**
[figure not shown]
**Trial flowchart**. This figure provides an overview of the participant flow.

### Analysis

To examine hypotheses 1 (that PA and energy expenditure will be reduced when children have access to traditional electronic games) and 2 (that PA and energy expenditure will be greater with new active electronic games, but still less than no games) a 4 (baseline and 3 game conditions) × 2 (sexes) repeated measures ANCOVA analysis with pre-specified contrasts will be conducted for each PA and energy expenditure variable. Prior game experience will be used as a covariate. A critical alpha level of 0.01 will be used to balance type 1 and type 2 errors.

To assess hypothesis 3 (that there will be a stronger effect on children with poor coordination skills, high adiposity, poor social confidence, more positive attitudes to technology and less positive attitudes to PA), separate multiple linear regression analyses for both traditional sedentary electronic and new active electronic games will examine the importance of individual characteristics on activity levels (total minutes of overall moderate/vigorous PA). Sex and amount of moderate/vigorous PA at the end of the no game period will be included as baseline covariates for the assessment of the independent effect on PA of; motor competence, adiposity, perceived athletic competence and attitudes to technology. To assess if individual characteristics may impact differently upon the relationship between PA and traditional sedentary electronic versus PA and new active electronic games, beta coefficients and associated 95% confidence intervals, and proportions of total variance explained by these variables, will be compared between the two models.

To assess hypothesis 4 (that all electronic games will displace active non-electronic leisure activities) the impact of the three study conditions on time spent in four outside school activities (reading, watching TV, using computers, playing sports and non-organised physical activity) will be examined using a 3 (no electronic games, traditional electronic games, active electronic games) ×2 (sex) repeated measures MANOVA with weekly minutes in each activity as the dependent variables.

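### The primary repeated measures ANCOVA has no period or season term and treats the unrandomised baseline as a fourth condition level, which gives away precision in a three-period crossover

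*Protocol article*

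**What the plan says.** The Analysis section states that, for each activity and energy expenditure variable, "a 4 (baseline and 3 game conditions) × 2 (sexes) repeated measures ANCOVA analysis with pre-specified contrasts will be conducted". On covariates it says "Prior game experience will be used as a covariate", and on the significance level "A critical alpha level of 0.01 will be used to balance type 1 and type 2 errors". It names no term for period, order or season.

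Season appears under the Covariates heading, with the remark that earlier research found summer and winter activity to differ, and to differ by sex. The stated handling is by design: "The potential seasonal effect will be allowed for in the design by having a balanced ordering of game conditions", together with staggered starts. The Procedure section gives four sets of the six possible orders in each yearly cohort of 24, so 12 children per order over three years. Trial flow places the baseline assessment before the first condition for every child.

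On data completeness the Participants section says "We [51] have had a compliance rate of 95% for DLW data collection and 92% for accelerometry", and adds an allowance of 10% attrition.

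**The concern.** A three-period crossover compares each child with himself or herself at different times. Follow-up is 10 days plus 3 × 8 weeks, about 25 weeks, which is long enough for activity to shift with season and with elapsed time. When every order is equally frequent, such shifts cancel from the average contrast. They do not cancel from the spread of the within-child differences, and a model without a period or season term counts that spread as error. The one covariate that is named does not vary within a child, so as a main effect it cannot take this variation out.

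Two further features follow from the four-level factor.

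- The overall condition test can be significant merely because the baseline week differs from the rest, through timing or through the child's own usual games. Hypotheses 1 and 2 compare only the three game conditions, and the same section uses a three-level factor for hypothesis 4.
- Classical repeated measures ANCOVA needs a value in every cell, so a child without a valid baseline week would not contribute to a contrast between two conditions in which that child was measured.

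At stake is precision on the primary contrasts at the strict 0.01 level.

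**Working it through.** **Inputs.** From Participants: 72 children; a 15-minute difference; SD 30 minutes; stated power 0.986 at alpha 0.05 and 0.943 at 0.01; 92% accelerometry compliance; 10% attrition. From Analysis: alpha 0.01. From Procedure: six orders, equally frequent. Tests are taken as two-sided, since the protocol does not say. The documents give no period or season effect in minutes, so those sizes are assumed below.

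**1. The plan's own figure.** Paired t test with noncentrality 15/30 × √72 = 4.24 on 71 degrees of freedom: power 0.987 at 0.05 and 0.941 at 0.01. Both agree with the stated figures. They therefore treat 30 minutes as the SD of the within-child difference and use all 72 children. Reading 30 as the SD of a single occasion (SD of difference 42.4) gives 0.841 and 0.638, which do not match.

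**2. Incomplete weeks, alpha 0.01, SD 30.**

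| Assumption | Children used | Power |
|---|---|---|
| None missing | 72 | 0.941 |
| 92% is a per-child rate (72 × 0.92 = 66.2) | 66 | 0.916 |
| 10% attrition (72 × 0.90 = 64.8) | 64 | 0.906 |
| 92% per week, independent, three condition weeks (72 × 0.92³ = 56.1) | 56 | 0.854 |
| 92% per week, independent, four weeks (72 × 0.92⁴ = 51.6) | 51 to 52 | 0.809 to 0.819 |

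In the independent per-week case, requiring the baseline week as well costs about 5 children and 4 to 5 points of power.

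**3. Period variation left in the error.** Let activity shift by h minutes per period, equally for all children. Two given conditions lie in adjacent periods in four of the six orders (difference ±h) and in periods 1 and 3 in the other two (±2h). The mean square added to the within-child difference is (4h² + 2(2h)²)/6 = 2h².

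- If the 30 minutes excludes period effects and h = 10: SD = √(900 + 200) = 33.2, power 0.88 with 72 children.
- Same, h = 15: SD = √(900 + 450) = 36.7, power 0.79.
- If the 30 minutes already contains a step of h = 10: adjustment lowers the SD to √(900 − 200) = 26.5, and power rises from 0.94 to 0.98.

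**4. Plan against alternative, by simulation** (1,200 runs per setting, 12 children per order, SD of difference 30 before any period shift, alpha 0.01). The plan is represented by a paired contrast in children with all four weeks and no period term. The alternative is a child + condition + period model on all available condition weeks; no separate season term was simulated.

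| Weeks valid | Step per period | Plan | Alternative |
|---|---|---|---|
| All | 0 | 0.95 | 0.95 |
| All | 10 min | 0.90 | 0.95 |
| 97.5%, independent (about 65 complete) | 0 | 0.91 | 0.94 |
| 97.5%, independent | 10 min | 0.87 | 0.95 |
| 92%, independent (about 51 complete) | 0 | 0.81 | 0.91 |
| 92%, independent | 10 min | 0.74 | 0.91 |

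With complete data and a 10-minute step, simulation gives 0.90 against 0.88 in step 3. The formula treats the period shift as random noise, whereas exact balance of orders keeps it out of the mean difference and only inflates the estimated error.

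**The case against.** The strongest reply is that season is dealt with by design. Orders are balanced and starts are staggered, so the absence of a model term is a choice and not an oversight. That stands as far as bias is concerned: with complete data the contrasts are unbiased. It does not answer the loss of precision.

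The second reply is that the planning SD is described thus: "If the variation in the PA level between repeated time points in each individual is normally distributed with standard deviation 30 mins". On its face this may already include variation between periods and seasons. If so, the stated power is not reduced, and adjustment is purely a gain. This also stands, and it is why both directions are shown. The period steps are assumed, and a common step for all children is only a rough stand-in for season when starts are staggered.

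Third, the hypotheses are tested by pre-specified contrasts. Contrasts among the three conditions do not use the baseline mean, so a reader who infers that the fourth level itself costs them power would be mistaken. Its cost comes only through requiring that week to be present.

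Other stronger readings are not supported either:

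- A rule that incomplete children are dropped. None is written; it is a consequence of the named method, and missing-data handling may sit in a plan that is not shown.
- A bias from dropout that differs by order. The protocol gives no ground for expecting it.
- A distorted condition test from an uncentred covariate. That depends on model coding that the protocol does not state.

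**Conclusion.** The point holds as one of precision and clarity. The named model omits period and season from a crossover of about 25 weeks and puts a never-randomised, always-first assessment into the condition factor. The four-level omnibus test is therefore not a clean test of game access, while the contrasts among the three conditions remain valid.

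The loss cannot be fixed at one figure. It is nil with complete data and no period effect. It is small with 64 to 66 complete children (0.91 to 0.92, still above the 0.9 claimed in the abstract). It reaches 0.81 to 0.82 only if the 92% applies to each week independently over four weeks, which the protocol does not say. The effect of leaving period out is either a fall from 0.94 to 0.88 or a forgone rise to about 0.98, for an assumed 10-minute step, depending on what the 30 minutes contains. A reader might infer that the trial is underpowered because of its model; the documents do not show that. They do show that a better analysis is available at almost no cost.

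**What to change.** For hypotheses 1 and 2, replace the four-level ANCOVA with a linear mixed model on the three randomised conditions, using every available condition week:

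- random effect for child;
- fixed effects for condition (three levels), period (1 to 3), season or calendar time of the assessment week, sex, and sex × condition;
- the pre-specified contrasts among conditions, at the 0.01 level already chosen.

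Keep baseline out of the condition factor; it can still be used to describe the sample. State that a child with a missing week contributes the remaining weeks.

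The cost is a change of wording and a few degrees of freedom. No new data are needed, because order and timing of assessments are known from the trial's own schedule. The change should be made before outcome data are examined.
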